# Evaluating the attrition, fabric integrity and insecticidal durability of two dual active ingredient nets (Interceptor^®^ G2 and Royal^®^ Guard): methodology for a prospective study embedded in a cluster randomized controlled trial in Benin

**DOI:** 10.1186/s12936-023-04708-x

**Published:** 2023-09-16

**Keywords:** Durability, Attrition, Fabric integrity, Bioefficacy, Experimental hut trials, Insecticide Treated Net, Pyriproxyfen, Chlorfenapyr, Alpha-cypermethrin, Dual active ingredient nets, Interceptor^®^, Interceptor^®^ G2, Royal Guard^®^

## Abstract

**Background:**

Following the World Health Organization (WHO) endorsement of dual active ingredient (AI) nets, an increased uptake of pyrethroid-chlorfenapyr and pyrethroid-pyriproxyfen nets is expected. Studies evaluating their physical and insecticidal durability are essential for making programmatic and procurement decisions. This paper describes the methodology for a prospective study to evaluate the attrition, fabric integrity, insecticidal durability of Interceptor^®^ G2 (alpha-cypermethrin-chlorfenapyr) and Royal Guard^®^ (alpha-cypermethrin-pyriproxyfen), compared to Interceptor^®^ (alpha-cypermethrin), embedded in a 3-arm cluster randomized controlled trial (cRCT) in the Zou Department of Benin.

**Methods:**

Ten clusters randomly selected from each arm of the cRCT will be used for the study. A total of 750 ITNs per type will be followed in 5 study clusters per arm to assess ITN attrition and fabric integrity at 6-, 12-, 24- and 36-months post distribution, using standard WHO procedures. A second cohort of 1800 nets per type will be withdrawn every 6 months from all 10 clusters per arm and assessed for chemical content and biological activity in laboratory bioassays at each time point. Alpha-cypermethrin bioefficacy in Interceptor^®^ and Royal Guard^®^ will be monitored in WHO cone bioassays and tunnel tests using the susceptible *Anopheles gambiae* Kisumu strain. The bioefficacy of the non-pyrethroid insecticides (chlorfenapyr in Interceptor^®^ G2 and pyriproxyfen in Royal Guard^®^) will be monitored using the pyrethroid-resistant *Anopheles coluzzii* Akron strain. Chlorfenapyr activity will be assessed in tunnel tests while pyriproxyfen activity will be assessed in cone bioassays in terms of the reduction in fertility of blood-fed survivors observed by dissecting mosquito ovaries. Nets withdrawn at 12, 24 and 36 months will be tested in experimental hut trials within the cRCT study area against wild free-flying pyrethroid resistant *An. gambiae *sensu lato to investigate their superiority to Interceptor^®^ and to compare them to ITNs washed 20 times for experimental hut evaluation studies. Mechanistic models will also be used to investigate whether entomological outcomes with each dual ITN type in experimental hut trials can predict their epidemiological performance in the cRCT.

**Conclusion:**

This study will provide information on the durability of two dual AI nets (Interceptor^®^ G2 and Royal Guard^®^) in Benin and will help identify suitable methods for monitoring the durability of their insecticidal activity under operational conditions. The modelling component will determine the capacity of experimental hut trials to predict the epidemiological performance of dual AI nets across their lifespan.

## Background

Insecticide-treated nets (ITNs) are the main malaria control and prevention intervention with over two and a half billion nets distributed globally between 2004 and 2021 [1]. Pyrethroids were for almost 3 decades the only insecticide class used on ITNs due to their safety profile, low cost and rapid activity against susceptible malaria mosquitoes. Modelling studies indicated that the reductions in malaria burden seen between the years 2000–2015 were largely due to large scale deployment of these nets especially in moderate to high transmission settings [2]. However, progress against malaria has stalled in recent years which is mostly attributed to stalling funding and the emergence, rapid spread and increasing intensity of resistance to pyrethroids in malaria vector mosquitoes across Africa [1, 3, 4], that undermines the impact of pyrethroid-only ITNs.

In response to the threat of pyrethroid-resistance, dual active ingredient (AI) ITNs treated with a mixture of a pyrethroid and a non-pyrethroid insecticide or compound to which local vector populations are largely susceptible have been developed for malaria vector control. Three new ITN types, pyrethroid-piperonyl butoxide (PBO), pyrethroid-chlorfenapyr and pyrethroid-pyriproxyfen ITNs, were recently added to the World Health Organization (WHO) list of prequalified vector control products after demonstrating improved impact against pyrethroid-resistant malaria vectors compared to pyrethroid-only nets [5]. Pyrethroid-PBO ITNs were the first new generation ITN class to further demonstrate improved public health value for control of clinical malaria compared to pyrethroid-only nets in cluster randomized controlled trials (cRCT) [6, 7] and based on these findings, they were conditionally recommended by the WHO for deployment in lieu of pyrethroid-only nets in pyrethroid-resistant areas in 2017 [8, 9]. Pyrethroid-chlorfenapyr and pyrethroid-pyriproxyfen ITNs are currently being evaluated in cRCTs in Benin and Tanzania for their improved public health value compared to pyrethroid-only nets over 3 years of operational use [10]. Based on results up to 24 months post-ITN distribution from these trials [11, 12], the WHO has recently released a strong recommendation for pyrethroid-chlorfenapyr ITNs over pyrethroid-only nets and a conditional recommendation for pyrethroid-pyriproxyfen nets over pyrethroid-only ITNs for malaria control in areas where vectors have become resistant to pyrethroids [9].

Following the WHO recommendation, an increased uptake of pyrethroid-chlorfenapyr and pyrethroid-pyriproxyfen nets is expected in the coming years. However, to be considered long-lasting, new ITNs need to be evaluated for their physical and insecticidal durability over 3 years of operational use [13–15]. Studies have shown that the durability of ITNs may vary widely from one community to another and between different product brands [16, 17]. ITN durability studies are useful for planning the replacement of worn-out nets and making programmatic and procurement decisions [14]. Modelling studies have suggested that ITNs are discarded more quickly than the 3 years presumed by country policies, and this is driven by several factors including the physical durability of the ITN brand [18]. Current WHO guidelines for assessing the attrition, fabric integrity, chemical content and insecticidal durability of ITNs under operational use [13, 15] were developed when pyrethroids were the only insecticides applied on ITNs and will need to be updated to cover new dual AI ITNs. This will require the development of standardized methods for assessing the insecticidal durability of non-pyrethroid insecticides like chlorfenapyr and pyriproxyfen on nets. Unlike pyrethroids that knockdown and kill mosquitoes, chlorfenapyr is a pyrrole insecticide that acts on the insect mitochondria to slowly induce death [19], while pyriproxyfen is an insect growth regulator that sterilizes adult female mosquitoes leading to a substantial reduction in offspring [20, 21]. Laboratory bioassay methods and strains used for assessing their bioefficacy on ITNs must, therefore, be aligned with the mode of action of these insecticides. In addition to bioassays (cone bioassays and tunnel tests), experimental hut trials have also been proposed as a suitable method for investigating the insecticidal durability of ITNs under operational conditions [22, 23]. Using hut trials, ITNs can be assessed against wild free-flying mosquito vectors providing more realistic estimates of their capacity to provide personal and community protection to householders as they age.

Experimental hut trials are typically used for assessing the entomological efficacy and wash resistance of ITNs under semi-field conditions for the WHO prequalification and for determining the non-inferiority of new ITN products to a similar product that has demonstrated empirical evidence of improved epidemiological impact in cRCT [13, 24]. For such studies, nets are artificially aged by washing up to 20 times to mimic naturally aged nets at the end of their operational life (3 years) and their entomological performance in experimental huts is used as a proxy for their disease control capacity. Cluster randomized controlled trials are the gold standard evidence for disease control interventions, however, because they are expensive and time consuming, hut trials have been used as a potentially more cost-effective high throughput alternative to support policy and decision-making to guide vector control product uptake [24, 25]. Given the increasing importance of experimental hut trials in the vector control product development process, studies establishing their capacity to predict the epidemiological performance of vector control products in cRCT are essential. This will ideally require the generation of experimental hut data alongside cRCT, which unfortunately has not been done in the past. Recent studies have indicated the capacity of mechanistic malaria transmission dynamics mathematical models to reliably predict the epidemiological performance of current widely used pyrethroid-only nets using data derived from experimental hut trials [25]. As the demand for dual AI ITNs increases, it is essential to establish the capacity of experimental hut data to predict their epidemiological performance to help speed up product development and decision-making for their deployment. The on-going cRCT in Benin provides a unique opportunity given that hut trials can be performed in parallel within the study area of the cRCT trial, facilitating modelling studies to investigate correlations between entomological data and epidemiological performance with clinical malaria endpoints.

This paper describes the methodology for a prospective longitudinal study investigating the attrition, physical and insecticidal durability of two dual AI ITNs (Interceptor® G2 and Royal Guard^®^) compared to a pyrethroid-only ITN (Interceptor^®^), embedded in a cRCT in Benin. We also discuss key issues around the evaluation of the insecticidal durability of dual AI ITNs. Prospective follow up surveys will be used to assess ITN attrition and fabric integrity and modified laboratory bioassays and experimental hut trials to evaluate the durability of the insecticidal efficacy of the non-pyrethroid component of both types of dual AI ITNs over 3 years of household use during the cRCT. Experimental hut trials will also be performed to investigate the capacity of ITN washing following standard WHO ITN evaluation procedures to predict the performance of naturally aged field nets of each ITN type. Finally, mechanistic models will be used to investigate whether entomological outcomes with each dual ITN type from hut trials can be used to predict their epidemiological performance in the cRCT.

## Overall aim of the study

To assess the physical and insecticidal durability of two dual AI nets; Interceptor^®^ G2 (alpha-cypermerthrin plus chlorfenpayr) and Royal Guard^®^ (alpha-cypermethrin plus pyriproxyfen) compared to a standard alpha-cypermethrin only net (Interceptor^®^) over 3 years of community use during a randomized-controlled trial in the Zou Region of Benin.

## Study objectives

To determine the survivorship, attrition and fabric integrity of Interceptor^®^ G2 and Royal Guard^®^ compared to a standard alpha-cypermethrin-only net (Interceptor^®^) over 3 years of household use in communities in BeninTo investigate insecticidal activity and chemical content of Interceptor^®^ G2 and Royal Guard^®^ compared to Interceptor^®^ over 3 years of household use in communities in Benin.To investigate householders’ preferences and perceptions of the different ITN fabric types (polyethylene for Royal Guard^®^ and polyester for Interceptor^®^) and it’s impact on ITN retention over 3 years of use in communities in BeninTo compare the performance of nets washed 20 times for experimental hut trial evaluations to 3 year old field aged nets.To investigate correlations between the entomological performance in hut trials and the epidemiological performance of each ITN type in the cRCT in Benin using mathematical models.

## Methods

### Study arms

The study consists of three arms evaluating the durability of two dual AI ITNs (Interceptor^®^ G2 and Royal Guard^®^) compared to a standard pyrethroid-only ITN Interceptor^®^. Study nets are all blue, rectangular, and sizes of 1.8 m long, 1.8 m wide, and 1.8 m high (Interceptor^®^ and Interceptor^®^ G2) and 1.8 m long, 1.8 m wide, and 1.6 m high (Royal Guard^®^). A description of the specifications of the three ITN types is provided below:Interceptor^®^ G2 (BASF AGRO B.V.), is a WHO-prequalified 100-denier, polyester ITN coated with a mixture of alpha-cypermethrin and chlorfenapyr at target concentrations of 100 mg/m^2^ (± 25%) and 200 mg/m^2^ (± 25%), respectively. The bursting strength of the fabric is ≥ 405 kPa while the mass per unit area is 40 g/m^2^ (± 10%) for 100 denier yarn.Royal Guard^®^ (Disease Control Technologies, LLC, USA), is a WHO-prequalified 100-denier, polyethylene ITN incorporated with a mixture of alpha-cypermethrin and pyriproxyfen at target concentrations of 261 mg/m^2^ (± 25%) and 225 mg/m^2^ (± 25%) respectively. The bursting strength of the fabric is ≥ 405 kPa while the mass per unit area is 45 g/m^2^ (± 10%) for 150 denier yarn.Interceptor^®^ (BASF AGRO B.V.), is a WHO-prequalified 100-denier, polyester ITN coated with alpha-cypermethrin at target concentrations of 200 mg/m^2^ (± 25%). The bursting strength of the fabric is ≥ 405 kPa while the mass per unit area is 40 g/m^2^ (± 10%) for 100 denier yarn. Interceptor® is the control arm of the trial against which Interceptor^®^ G2 and Royal Guard® are compared.

### Study setting

This ITN durability study is embedded in a cRCT performed in the Cove, Zagnanado, and Ouinhi districts (COZO), of the Zou department of central Benin (7°11′N 1°59′E). The design of the cRCT has been published previously [10]. The study area consists of 123 villages with approximately 54,000 households and a population size of 220,000 inhabitants. Baseline studies performed in 2019 as part of the cRCT demonstrated a malaria prevalence of 43.5% [26] and high intensity of resistance to pyrethroids but no resistance to chlorfenapyr and pyriproxyfen in main malaria vectors in the study area; *Anopheles gambiae* and *Anopheles coluzzii* [27].

### Study design

The study area was divided into 60 clusters that were randomly assigned to the three arms of the cRCT using restricted randomization. Study nets are identical in appearance and participating households are blinded to the type of ITN they received. Field data collectors are also blinded to the allocation of households to the study arms. Ten clusters from each study arm have been randomly selected for the durability assessment (Fig. 1). Following ITN distribution, households in these clusters will be visited to mark and prospectively follow 2 separate cohorts of ITNs per arm (Cohorts 1 and 2) every 6–12 months to monitor their physical and insecticidal durability over a period of 36 months. Cohort 1 will consist of at least 750 nets from ~ 250 randomly selected households per arm (assuming 3 ITNs are distributed per household) from 5 study clusters per study arm. These nets will be followed for ITN survivorship and fabric integrity at 6-, 12-, 24- and 36-months post ITN distribution. Cohort 2 will consist of ~ 1800 nets per study arm from ~ 600 households from all 10 randomly selected clusters (60 households per cluster) per study arm to be withdrawn (and replaced with new nets) for assessment of insecticidal activity in laboratory bioassays and experimental hut trials, content of each active ingredient and for other studies. Cohort 1 and cohort 2 nets will receive separate identification numbers and would be sampled from different households to prevent the risk of destructive sampling of nets intended for ITN survivorship studies (cohort 1). Figure 2 provides a summary of the study design and studies to be performed at each timepoint.

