### Follow up surveys for cohort 1 nets

#### Follow-up for ITN attrition

All households in cohort 1 (at least 750 nets/arm) will be visited at 6-, 12-, 24- and 36-months post ITN distribution and nets assessed for attrition at each timepoint by recording the physical presence/absence of each net that was marked in the household. Where a net is not found, the householder will be asked about the reason for the loss of the net, e.g. given away, sold, stolen, worn out and disposed of. Any net which has never been used, will be recorded, and excluded from the analysis. During these surveys, a questionnaire adapted from WHO guidelines will be used to collect data on the number of washes and washing practices for the nets found in each household.

ITN retention may also be affected by householders’ preference of the fabric type used in the formulation of the net. A low preference for polyethylene nets has been previously observed in Benin by the National Malaria Control Programme (NMCP), which may differentially affect the retention of Royal Guard^®^ (polyethylene) compared to Interceptor^®^ and Interceptor^®^ G2 (polyester). As part of these follow up surveys, a short questionnaire will be administered to assess householders’ perception of the ITN fabric types and changes in size of each ITN type to determine whether this may have impacted their decision to discard the net. A subset of ITNs of each type at 0, 12, 24 and 36-months post-distribution (minimum 100 per ITN type) will also be measured to directly examine changes in ITN size over time.

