## Discussion

This paper describes the methodology for evaluating the physical and insecticidal durability of two dual AI ITNs (Interceptor^®^ G2 and Royal Guard^®^) as part of an ongoing cRCT in Benin. Both nets are being compared to a WHO prequalified alpha-cypermethrin net (Interceptor^®^). By investigating the attrition and fabric integrity of the study nets, we will generate data needed for planning their replacement and for making programmatic and procurement decisions [14] once they are deployed more widely. Previous studies have shown that householders distinguish between ITN products and tend to overwhelmingly prefer polyester ITNs over polyethylene ITNs [34]. By investigating householders’ preferences and perceptions of the different ITN fabric types used in the formulation of the study nets (polyethylene for Royal Guard^®^ and polyester for Interceptor^®^ G2 and Interceptor^®^), we will also provide more insights into how fabric type may affect ITN retention and overall impact in Benin.

Dual AI ITNs cost significantly more than standard pyrethroid nets due to the additional non-pyrethroid active ingredient on these nets. To ensure value for money, it is essential to closely monitor the insecticidal activity of the non-pyrethroid component in these nets using insecticide durability bioassays. Current WHO ITN insecticide durability guidelines were developed mostly for pyrethroid-only nets hence the methods and recommended strains were suited to their rapid mode of action [13]. We propose subtle modifications to these standard laboratory bioassay methods and to recently developed consensus SOPs [35] to facilitate monitoring of the insecticidal durability of chlorfenapyr in Interceptor^®^ G2 and pyriproxyfen in Royal Guard® while improving the efficiency of the bioassays. First, the mosquito strains used in laboratory bioassays with dual AI ITNs must allow assessment of the non-pyrethroid insecticide in the net without interference from the pyrethroid component. For assessment of pyriproxyfen in Royal Guard® for example, it is essential that enough blood-fed survivors are obtained post ITN exposure. By using a high intensity pyrethroid-resistant strain (*An. coluzzii* Akron) we will substantially reduce the toxicity and confounding effect of the pyrethroid allowing a more realistic assessment of the non-pyrethroid components.

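### Royal Guard differs from Interceptor in fabric and height, so blinding through identical appearance cannot be claimed for that comparison

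*Protocol article*

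**What the plan says.** Under Study design the protocol article makes two blinding statements. On nets and households: "Study nets are identical in appearance and participating households are blinded to the type of ITN they received". On staff: "Field data collectors are also blinded to the allocation of households to the study arms".

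Under Study arms, the features common to all nets are colour and shape: "Study nets are all blue, rectangular". The dimensions then diverge. Interceptor and Interceptor G2 have "sizes of 1.8 m long, 1.8 m wide, and 1.8 m high"; Royal Guard is "1.8 m long, 1.8 m wide, and 1.6 m high". Royal Guard is described as a "polyethylene ITN incorporated with a mixture of alpha-cypermethrin and pyriproxyfen", whereas both other nets are coated polyester.

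Fabric is also a subject of the study. The third objective concerns householders' perceptions of polyethylene and polyester and the effect on retention. The section on follow-up for attrition reports that "A low preference for polyethylene nets has been previously observed in Benin", says this may affect Royal Guard retention differentially, and plans a questionnaire on fabric type and changes in net size. The Discussion cites previous studies in which "householders distinguish between ITN products and tend to overwhelmingly prefer polyester ITNs over polyethylene ITNs".

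The section on household sensitization and marking says that each net will carry a handwritten code that identifies, among other things, its study arm.

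**The concern.** The article cannot describe all three nets as identical in appearance while specifying one of them in a different fibre and at a different height. Nor does that description sit well with an objective that needs householders to perceive the fibre.

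The cohort 1 outcomes that depend on human report or judgement are at stake. The householder reports why a net is missing, and under Statistical analysis the nets given away, sold or stolen are left out of functional survival. That report therefore decides which nets enter the analysis. The survey team counts and sizes holes with the net draped on a frame. If a reader takes these Royal Guard outcomes as blinded, a safeguard against reporting and observer bias is credited where the document does not establish it. This is also the comparison in which the article itself anticipates a fabric preference.

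**Working it through.** No sample size, power or error rate enters this point. The check sets the sections side by side.

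**1. Is the appearance claim consistent with the specifications?** All inputs are from Study arms.

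| Feature | Interceptor | Interceptor G2 | Royal Guard |
|---|---|---|---|
| Colour, shape | blue, rectangular | blue, rectangular | blue, rectangular |
| Fibre | polyester | polyester | polyethylene |
| Treatment | coated | coated | incorporated |
| Height | 1.8 m | 1.8 m | 1.6 m |
| Mass per unit area | 40 g/m² (± 10%) | 40 g/m² (± 10%) | 45 g/m² (± 10%) |

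- Interceptor and Interceptor G2 match on every row, so the claim is consistent with the specifications for that pair.
- Royal Guard is shorter by 1.8 − 1.6 = 0.2 m, and 0.2 / 1.8 = 11.1%.
- The mass tolerances overlap (36 to 44 g/m² and 40.5 to 49.5 g/m²), so mass alone need not separate the nets. The conclusion rests on fibre and height.

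**2. Who could notice?**

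- *Survey staff.* They spread each cohort 1 net over a frame in daylight and inspect the roof and every side. Fibre and height are in front of them. In addition, the code on the net identifies the arm, and the article does not say whether it is masked.
- *Households.* They live with the net and are asked about its fabric. Allocation is by cluster, so a household need not have another study net type at hand for comparison.

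**3. Which outcomes does this reach?**

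| Outcome | Source | Exposed? |
|---|---|---|
| Net present or absent | recorded at visit | little room for judgement |
| Reason for loss | householder report | yes |
| Functional survival | depends on reason for loss | yes, through that report |
| Hole number and size | scored by survey team | yes |
| Chemical content, laboratory bioassays, hut trials | cohort 2 nets, other procedures | not reached by this point |

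**4. Fabric area, kept separate.** Roof plus four sides from the nominal dimensions:

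- Interceptor and Interceptor G2: 1.8 × 1.8 + 4 × 1.8 × 1.8 = 3.24 + 12.96 = 16.20 m²
- Royal Guard: 1.8 × 1.8 + 4 × 1.8 × 1.6 = 3.24 + 11.52 = 14.76 m²
- Difference: 1.44 m², and 1.44 / 16.20 = 8.9% less for Royal Guard

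This is a difference in net size. It says nothing about how far knowledge of the arm might shift a report or a hole count.

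**The case against.** The strongest reply is that a visible difference is not the same as unblinding. The article says households are blinded to net type and collectors to allocation. A householder who sees a polyethylene net need not know the product or its active ingredient. This stands. A reader might infer that the Royal Guard arm is simply open-label; the documents do not support going that far. They support only that identical appearance cannot be the basis for blinding it.

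The evidence on preference is also indirect. The Discussion refers to previous studies and the attrition section to an earlier programme observation, and neither concerns these households. That limits what can be said about how they will react, but the contradiction between Study design and Study arms does not depend on it.

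Next, fabric preference is something the study sets out to measure. If households discard Royal Guard because they dislike polyethylene, that is a property of the product and not a bias. This stands too, so differences in retention and perception should not be counted as harm from failed blinding.

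Hole scoring uses defined size classes on assessment sheets, which limits discretion without removing it. Nowhere does the article say that Royal Guard results will be reported as blinded.

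A reader might also take the 8.9% as the size of the bias, or as an advantage to Royal Guard in hole area. It does not measure the former, and the latter requires damage to be uniform over the net, which no section states.

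**Conclusion.** The statement in Study design is wrong as written for Royal Guard, and the article's own specifications show it. Blinding by identical appearance cannot be claimed for Royal Guard versus Interceptor, above all for staff who handle and drape the nets. The consequence is confined to cohort 1: reported reason for loss, functional survival through it, and hole scoring should be read as not securely blinded in that comparison. No bias is shown and none can be sized from the document.

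On appearance, nothing contradicts the claim for Interceptor versus Interceptor G2. A reader might conclude that blinding is therefore assured for that pair. The documents do not go so far, because the arm code is on every net and its masking is not described.

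The conclusion assumes only that the fabrics and nominal heights under Study arms are correct.

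**What to change.** 1. In Study design, limit the statement on identical appearance to Interceptor and Interceptor G2, and say that Royal Guard is distinguishable by fabric and height.
2. Reconcile the statement on collector blinding with the code described under household sensitization and marking: say whether survey staff could read the arm from it, and word the claim to match.
3. When reporting Royal Guard against Interceptor, describe reason for loss, functional survival and hole scoring as not securely blinded. Present retention differences attributable to fabric preference as a product effect.
4. Optionally, and as a separate matter, add a sensitivity analysis of hole area with log fabric area as an offset, stating the uniform-damage assumption. It would not address blinding.

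The first three items cost only wording and a more modest blinding claim; the fourth is one extra model. Nets were distributed in 2020 and surveys were complete to 24 months at publication, so masking at those visits cannot be changed. Description and interpretation still can.
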